#### Semi-structured focus group interview with healthcare managers and practice consultants

We will conduct an online semi-structured focus group interview with 4–6 key healthcare managers and practice consultants within the field of physiotherapy. The managers were public and private physical therapy clinic managers and lead managers in local municipalities responsible for health and rehabilitation resources. Furthermore, we will invite practice consultants within physiotherapy from the Central Denmark Region. A semi-structured interview guide has been developed and key questions are included in Table 4.

**Table 4 Tab4:** Process evaluation domains, themes and key questions for an interview with healthcare managers

Domain	Theme	Questions
**Acceptability**	Experiences	What immediate thoughts do you have regarding the implementation of new interventions for citizens/patients in your organisation, or the organisations that you are involved with?
		What do you find most important when you decide or recommend if a new intervention should be implemented in your organisation, or the organisations that you are involved with?
		What strategies do you use when implementing or recommending new interventions to ensure that employees have the best prerequisites for following the new recommendations?
		What strategies do you use when implementing or recommending new interventions to ensure employees´ knowledge and skills?
	Priorities	How do you, in your organisation or the organisations you are involved with, decide if an intervention is relevant to implement?
		Do you, in your organisation or the organisations you are involved with, have any services where you can envision the MovetheHip intervention being added to the current treatment options?
**Implementation**	Context	Please tell me about a successful implementation
		Please tell me about a less successful implementation
	Knowledge	What knowledge about the MovetheHip intervention do you find most crucial to assess in terms of their relevance and benefits?
		- What type of evidence do you need?
	Context	What would support a successful implementation of the MovetheHip intervention?
		What would prevent a successful implementation of the MovetheHip intervention?

This focus group interview will explore intervention acceptability regarding how healthcare managers and consultants decide if an intervention is relevant and beneficial in their organisation; specifically, what information or evidence they need, and how they prioritise interventions and provide the necessary financial resources. Furthermore, the interview will explore their experiences with inter-organisational behaviour change. The data from the interviews with the healthcare managers may add to our understanding of what type of information healthcare managers consider essential. This understanding is important should they consider supporting a forthcoming implementation of this intervention, provided it proves to be effective and cost-effective.

### Quantitative data analysis

Descriptive statistics will be used on implementation data; normally distributed continuous data will be reported as means with standard deviations and categorical data will be reported as numbers and proportions. Mechanisms of change will be examined by linking intervention functioning (qualitative data) to mean changes in health outcomes. Specifically, mean changes in health outcomes will be calculated in normally distributed data using descriptive statistics. Furthermore, we will explore the possibility of dichotomising data on intervention dose into low versus high. Reach will be examined by describing baseline characteristics within each dose group using descriptive statistics.

Additional explorative analyses will be performed. To examine the implementation, we will explore if the dose is associated with changes in health outcomes, using simple linear regression models with doses as independent variables and changes in health outcomes as dependent variables. Furthermore, in a repeated measurement analysis using a mixed-effects model, an explorative analysis will be undertaken to determine if the reason for deselecting surgery (i.e. dichotomised into the surgeon’s or participant’s decision) moderates dose changes as part of the examination of acceptability. In the model, participants will be the random effects with a fixed factor for group and time and the corresponding interaction (group × time), adjusted for baseline values. Statistical significance is considered to have been achieved at *p* < 0.05, and the Stata 17 (StataCorp, College Station, TX, USA) software package is used for the data analyses.

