**Methods:**

Two hundred trial participants aged 18–50 years will be recruited from a University Hospital in Denmark and randomised to the intervention or control group. Approximately ten providers will deliver the intervention. The process evaluation adopts a concurrent mixed-methods design. The implementation will be assessed using self-report questionnaires (at baseline and 6-month follow-up), training records and semi-structured focus group interviews with intervention providers (*n* = 10) and healthcare managers (*n* = 4–6). The mechanisms of change will be explored through semi-structured one-to-one interviews (at baseline and 6-month follow-up) with 15–20 purposefully sampled participants and by measuring changes in health outcomes (self-reported pain, physical functioning and quality of life completed at baseline and at 3- and 6-month follow-up). Additionally, change will be measured through an explorative examination of associations between dose and change in health outcomes, applying simple linear regression models. The acceptability of the intervention and the influence of contextual factors will be explored through one-to-one participant interviews and focus group interviews with 4–6 healthcare managers. The interviews will focus on expectations, experiences, events, personal understandings and interaction with interpersonal and organisational aspects. Interview data will be analysed using theoretical thematic analyses, and findings will be merged with quantitative data and reported jointly on a theme-by-theme basis.

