**Acceptability**	How do contextual factors relate to perceptions of a forthcoming implementation?	Focus group interview	Interview led by the last author	When 50% of the participants have been recruited	Healthcare managers and practice consultants (*n* ≈ 4–6)
**Acceptability** **(explorative)**	Does the reason for deselecting surgery moderate dose?	Online rating scale^b^	Self-report: exercise dose	Six months	Participants (*n* ≈ 100)
		Online record	Clinician registration: reason to deselect surgery	Baseline	Participants (*n* ≈ 100)
**Mechanisms of change**	Does intervention functioning relate to a change in health outcomes?	1:1 semi-structured interviews	Interview led by the first author	Baseline and 6 months	Participants (*n* ≈ 15–20)
		Online PROM^1^	Self-report: pain, physical functioning and QOL	Baseline, 3 and 6 months	Participants (*n* ≈ 100)
**Mechanisms of change**	How do contextual factors structure intervention functioning?	1:1 semi-structured interviews	Interview led by the first author	Baseline and 6 months	Participants (*n* ≈ 15–20)

*PROM* Patient-reported outcome measure, *QOL* Quality of Life, *VAS* Visual analogue scale

^a^Self-reported pain, physical functioning in sports and recreation and quality of life measured by the Copenhagen Hip and Groin Outcome Score and physical functioning measured with the Short version of the International Hip Outcome Tool

^b^Exercise Adherence Rating Scale

^c^A senior lecturer, the first and fourth authors

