## Methods

### Overarching research design

The overarching study design is a parallel-group superiority RCT with integrated process and health economic evaluation [21] designed in line with MRC Guidance principles [20]. The RCT follows the Standard Protocol Items: Recommendations for Interventional Trials statement [27] (Additional file 1). The process evaluation will follow a concurrent design with data collection and analyses being completed during similar time frames [28] (Fig. 2). The trial participants will be 18–50 years old and will have radiographically verified acetabular dysplasia and have experienced hip pain for a minimum of 3 months [21]. The participants will be dichotomised into either eligible but unwilling to undergo a PAO or not eligible for the PAO [21]. Further information on the study setting, eligibility criteria, sample size, etc., is reported in the RCT protocol [21]. In brief, to obtain sufficient statistical power, the RCT will recruit a minimum of 85 participants to the intervention group and 85 to the control group (usual care). Usual care includes one oral consultation provided by the first author on self-management of hip symptoms, including advice about staying physically active and exercising and, if relevant, advice to lose weight [21]. All intervention group participants will be included in the generation of process data. The RCT aims to investigate the effectiveness and cost-effectiveness of exercise and patient education compared with usual care [21].

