### Mechanisms of change

Mechanisms of change will be assessed by analysing how participants interact with the intervention activities to facilitate change in health outcomes. We will examine if autonomy, competence and relatedness relate to motivation and change in health outcomes and study the influence of contextual factors [22, 23].

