#### Semi-structured interviews with participants

Participants will be invited to participate in semi-structured one-to-one interviews by purposeful sampling at baseline and at the 6-month follow-up. Sampling will take into account factors such as gender, age, employment status and reason for not undergoing surgery. Data saturation will be checked prospectively, and further data collection will be undertaken if needed. The mode of the interviews will be either physical or via a video connection according to the participant’s preference. Baseline interviews will focus on previous experiences and expectations to changes and behaviour (degree of external, integrated or internal motivation) and the influence of personal, interpersonal and organisational contextual factors. The 6-month follow-up interviews will focus on experiences with the intervention, its acceptability and the participant’s behaviour (degree of external, integrated or internal motivation), as well as the influence of personal, interpersonal or organisational contextual factors. A semi-structured interview guide is developed and key questions are included in Table 2. As mentioned above, the interview data will be used to examine the underlying mechanisms of change.

**Table 2 Tab2:** Process evaluation domains, themes and key questions for semi-structured one-to-one interviews with participants

Domains	Theme	Questions

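### Mechanisms of change are examined by linking 15–20 interviews to the uncontrolled mean change of the whole intervention arm, which cannot show whether need satisfaction or motivation relates to outcome

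*Protocol article*

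**What the plan says.** The aim is relational. Under Mechanisms of change the article states: "We will examine if autonomy, competence and relatedness relate to motivation and change in health outcomes". Table 1 puts the matching research question as "Does intervention functioning relate to a change in health outcomes" and names two sources for it: one-to-one interviews at baseline and 6 months with about 15–20 participants, and outcome questionnaires at baseline, 3 and 6 months from about 100.

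The method is in Quantitative data analysis: "Mechanisms of change will be examined by linking intervention functioning (qualitative data) to mean changes in health outcomes". The next sentence fixes the statistic: "Specifically, mean changes in health outcomes will be calculated in normally distributed data using descriptive statistics".

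Overarching research design identifies the 100 as the intervention arm: "All intervention group participants will be included in the generation of process data". Data integration then merges the two strands after separate analysis, theme by theme, and judges whether they agree, add to each other or conflict.

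**The concern.** Asking whether one thing relates to another needs variation on both sides. The interviews vary between people, but the arm mean does not. Nothing in the stated analysis connects what an interviewee said with how that interviewee's own scores moved.

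The mean change is also uncontrolled. It contains whatever would have happened under usual care, together with any effect of the intervention. Usual care here is not inert: Overarching research design describes a consultation on self-management that includes advice on activity and exercise. If positive interviews are woven together with an arm that improved, the two will look mutually confirming even if the control arm improved just as much. At stake is the third overarching research question, whether the intervention works through the proposed mechanisms.

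**Working it through.** The plan has no figure of its own to reproduce on this point. The check sets the sections side by side, with short arithmetic.

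**1. Who is on each side of the link.** The abstract gives the trial total ("Two hundred trial participants aged 18–50 years will be recruited from a University Hospital in Denmark and randomised to the intervention or control group") and the interview sample ("with 15–20 purposefully sampled participants"). Equal allocation is implied by Table 1: 200 / 2 = 100 in the intervention arm. Interviewees are therefore 15/100 = 15% to 20/100 = 20% of the people whose mean is used.

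**2. What the mean can show.** There are three HAGOS scores (pain, sport and recreation function, quality of life) and the iHOT-12. With changes from baseline to 3 and to 6 months, that is 4 × 2 = 8 arm means. Each is a constant across participants. Suppose half the arm, with needs met, changes by 2m and the other half by 0: the mean is (2m + 0)/2 = m. Suppose instead everyone changes by m regardless of needs: the mean is again m. The proposed mechanism and its absence give the same number.

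**3. Whether another planned analysis fills the gap.** The listed data sources include no questionnaire on need satisfaction or motivation. These constructs appear only in interviews and focus groups. The regression of outcome change on dose is at person level, but its predictor is dose and it is assigned to implementation.

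**4. What the missing control arm can hide.** Write the arm's mean change as c + e, where c is the change under usual care and e the true effect. The non-specific share is c/(c + e). The documents give neither value, so both are assumed:

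| e (points) | c = 0 | c = 2.5 | c = 5 | c = 10 |
|---|---|---|---|---|
| 10 | 0% | 20% | 33% | 50% |
| 5 | 0% | 33% | 50% | 67% |
| 0 | – | 100% | 100% | 100% |

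**5. What a person-level link could carry.** Assume needs are coded to a score and correlated with the interviewee's own change. The smallest correlation significant at two-sided 0.05 is r = t/√(n − 2 + t²), with t the 97.5% point on n − 2 degrees of freedom. The true correlation needed for 80% power is tanh[(1.960 + 0.842)/√(n − 3)].

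- n = 15: r = 2.160/√(13 + 4.667) = 0.51; needed for 80% power, tanh(2.802/√12) = 0.67.
- n = 20: r = 2.101/√(18 + 4.414) = 0.44; needed for 80% power, tanh(2.802/√17) = 0.59.

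Only strong associations would be detectable, so the pairing is descriptive and should be labelled exploratory.

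**The case against.** The strongest defence is that this is a mixed-methods process evaluation. Theme-level weaving does not formally require person-level pairing. Effectiveness is left to the randomised comparison, and use of the findings for optimisation is conditional on proven effectiveness. Integration expressly allows for discordance, and the coding framework is built blind to the RCT findings. A condensed article may also omit how the integrated results will be displayed.

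Much of this stands, and it rules out several stronger readings that a reader might infer:

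- *That the plan treats natural course as intervention functioning.* It does not. Functioning is defined as the interview data, and nowhere is the mean change called an effect. The risk is misattribution at the interpretation stage.
- *That the two strands share no common unit.* They do. Interviewees belong to the arm whose outcome scores and dose are collected. The participant is available as the unit but is not used.
- *That the interview sample will lack low-dose or non-improving people.* The documents do not show this. "Sampling will take into account factors such as gender, age, employment status and reason for not undergoing surgery" is an open list, dose and response do not exist at the baseline interview, and further data collection is allowed if saturation is not reached.
- *That a definite number of points of spurious gain can be stated.* The article gives no standard deviation, no retest correlation and no score threshold for entry, so no such figure can be derived.

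The defence does not remove the core. The article does not leave the mechanism analysis open: it names the method and the statistic, and that statistic cannot answer the question. A proven overall effect would still not show that it arose through the proposed mechanisms.

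**Conclusion.** The point holds in a limited form. Followed as written, the quantitative side of the mechanism analysis cannot show whether autonomy, competence, relatedness or motivation relates to change in health outcomes. It also offers no guard against crediting the intervention with improvement that usual care would share. This affects one of the three overarching research questions and leaves the trial's effectiveness result alone.

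The first part follows from the design and needs no assumed values. The size of the second is unknown: it runs from nothing, if the control arm does not change, to the whole of the arm's improvement, if there is no true effect. The conclusion assumes that the 100 in Table 1 are the intervention arm, as Overarching research design implies, and that the full RCT protocol, not shown here, does not specify a different mechanism analysis.

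**What to change.** Amend Quantitative data analysis and Data integration in two places.

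1. Pair each interviewee's themes with that person's own HAGOS and iHOT-12 changes and own dose in a joint display. Contrast those who improved with those who did not, and label the result exploratory because it rests on 15–20 people.
2. At integration, after coding is complete so that the blinding to RCT findings is kept, show the control-arm change and the randomised between-arm difference at 3 and 6 months beside the intervention-arm means. Interpret mechanisms against that difference.

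The first change uses data already planned for every intervention participant. The second assumes that the control arm completes the same questionnaires at the same times; the article implies this through the randomised comparison but leaves the detail to the RCT protocol. No additional interviews are needed. The cost is a little more analysis and reporting, and a more cautious statement about mechanisms.

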#### Online participant survey

Participants will enter baseline data using a survey option in a Research Electronic Data Capture (REDCap) database. Baseline process data include sex, age, duration of hip symptoms, educational level, employment status, cohabiting status and level of physical activity [21]. These data will be used to examine intervention reach as aforementioned.

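### The exploratory dose-outcome analysis rests on one unadjusted regression of change on self-selected dose; a baseline-adjusted model should be reported beside it

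*Protocol article*

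**What the plan says.** The Quantitative data analysis section opens its second paragraph with "Additional explorative analyses will be performed". The first of these is the dose analysis, whose aim is worded as an association: "we will explore if the dose is associated with changes in health outcomes". The method for it is fixed in the same sentence, namely "using simple linear regression models with doses as independent variables and changes in health outcomes as dependent variables". The abstract's Methods paragraph names the same technique: "applying simple linear regression models". No covariate is mentioned in either place.

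The next analysis in that section, a mixed model on the reason for deselecting surgery, is "adjusted for baseline values". The paragraph closes with one significance rule, "Statistical significance is considered to have been achieved at" p < 0.05, and does not exempt the dose models.

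The dose analysis uses the intervention arm: "All intervention group participants will be included in the generation of process data". Table 1 puts this at about 100 participants. Candidate covariates are already in the data set. The Online participant survey section states: "Baseline process data include sex, age, duration of hip symptoms, educational level, employment status, cohabiting status and level of physical activity". Table 1 adds the outcome scores at baseline, 3 and 6 months and the reason for deselecting surgery at baseline.

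**The concern.** Dose is not randomised. It is what each participant managed to do, measured by sessions completed and by the adherence scale. A change score contains the baseline score with a negative sign, so it tends to fall as baseline rises whenever follow-up regresses on baseline with a slope below 1. If people who start better or worse also train more or less, a regression of change on dose alone can pick up that pattern and show it as a dose slope.

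The article itself treats a link between starting status and dose as possible. Table 1 asks whether baseline characteristics differ between high-dose and low-dose participants. The patient education section has participants adapt the exercises to their functioning. The Discussion expects some to struggle to keep up the dose. The plan therefore looks at this link under reach and leaves it out of the dose-outcome model. At stake is whether an exploratory dose association can be interpreted: it could be produced by baseline differences, or a real one could be masked.

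**Working it through.** The article gives no error rate, SD or correlation for this analysis, so there is no figure to reproduce. The only document inputs are n of about 100 (Table 1), about ten providers (abstract), and the 0.05 threshold (two-sided assumed). Everything else below is an assumption, shown as a range.

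**Set-up.** B is the baseline score, F the follow-up score and D the dose. B and F both have SD 20, ρ = corr(B, F) is 0.5 to 0.7, and r = corr(B, D) is 0 to 0.3. Dose has no true effect.

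**Case 1: dose follows the observed baseline score.** F = ρB + error, so change = F − B = −(1 − ρ)B + error.

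- Slope of change on dose, in points per SD of dose = −(1 − ρ) × r × 20
- Variance of change = 2(1 − ρ) × 400
- Standard error = √[(variance of change − slope²)/98]
- The false-positive rate follows from the ratio of slope to standard error (non-central t, 98 df).

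| ρ | r | Slope | Standard error | Ratio (absolute) | False positives |
|---|---|---|---|---|---|
| any | 0 | 0 | – | 0 | 5% |
| 0.7 | 0.1 | −0.3 × 0.1 × 20 = −0.6 | √[(240 − 0.36)/98] = 1.56 | 0.38 | 6.7% |
| 0.5 | 0.2 | −0.5 × 0.2 × 20 = −2.0 | √[(400 − 4)/98] = 2.01 | 1.00 | 16.7% |
| 0.5 | 0.3 | −0.5 × 0.3 × 20 = −3.0 | √[(400 − 9)/98] = 2.00 | 1.50 | 31.9% |

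Simulation (10,000 runs per setting) gave 6.7%, 16.7% and 32.4% for the last three rows. Regressing F on D and B in the same data gave 4.6% to 5.4% over the settings run. The sign shown is for dose rising with the baseline score; it reverses if dose falls with it.

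**Case 2: dose follows a stable underlying severity.** B and F are two noisy readings of that severity, so D correlates r with each. The two contributions cancel in F − B, and the change-score slope is 0. The slope on dose in the baseline-adjusted model is 20 × r(1 − ρ)/(1 − r²).

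| ρ | r | Adjusted slope | False positives, adjusted | False positives, change score |
|---|---|---|---|---|
| 0.7 | 0.1 | 20 × 0.03/0.99 = +0.6 | 7.4% | 5.1% |
| 0.5 | 0.2 | 20 × 0.10/0.96 = +2.1 | 21.7% | 5.0% |
| 0.5 | 0.3 | 20 × 0.15/0.91 = +3.3 | 44.8% | 4.9% |

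The rates are simulated, 10,000 runs each. For the same r, the two models err in opposite directions, each under its own case. If both must exclude zero in the same direction, the false-positive rate cannot exceed the lower of the two, which is about 5% in either case.

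**Providers.** With an even split, 100/10 gives m = 10 participants per provider. The variance factor from ignoring providers is 1 + (m − 1) × ICC of dose × ICC of outcome.

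- Dose ICC 0: factor 1.00, whatever the outcome ICC.
- Both ICCs 0.05: 1 + 9 × 0.0025 = 1.02, standard error × 1.01, false positives 5.3%.
- Dose ICC 0.20, outcome ICC 0.10: 1 + 9 × 0.02 = 1.18, standard error × 1.09, false positives 7.1% (6.1% in simulation).

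With independent provider effects on dose and outcome, the simulated slope bias was zero. Most planned sessions are at home: 8 supervised against 3 × 26 = 78, so 8/86 = 9% are supervised.

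**The case against.** The strongest reply is that the analysis is labelled exploratory, worded as an association and confined to one arm, and that swapping in baseline adjustment would not clearly improve it. Much of this stands. Case 2 shows that a change score can be the right choice and the adjusted model the wrong one. The documents do not say which mechanism applies, so they do not support simply replacing one model with the other.

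The label does not settle the matter, though. The article applies the 0.05 threshold to these models as well, and calling a slope an association does not remove the part created by baseline differences. Nor is this a detail left to a fuller document: the model is stated in two places as simple regression, which means one predictor.

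A reader might go further in three ways that the documents do not support:

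- That the slope will be biased. This needs a correlation between baseline score and dose, which no section gives. Table 1 only asks about it, and at r = 0 the bias is nil.
- That shared providers bias the dose slope. They do so only if provider effects on dose and on outcome are correlated. Otherwise they affect only the standard error, by about 0% to 9% over the assumed ICCs. The even split is itself an assumption, since student providers are replaced during the trial.
- That decisions on optimising the intervention rest on this slope. The Discussion gives that role to the process data as a whole, merged with the interviews.

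**Conclusion.** The concern holds in a limited form. The dose-outcome analysis offers a single unadjusted view of a self-selected exposure, although the data for a second view are collected and the neighbouring model is adjusted for baseline. If dose is correlated with the observed baseline score at 0.1 to 0.3, the slope can be off by about 0.6 to 3.0 points per SD of dose, with false positives of about 7% to 32% against a nominal 5%. These figures rest on the assumed SD of 20, baseline/follow-up correlation of 0.5 to 0.7, n = 100 and no true dose effect. At zero correlation, or if dose follows a stable underlying severity, the planned model is not biased in this way. Severity is minor to moderate: the analysis is exploratory and the randomised comparison is not affected.

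**What to change.** Keep the change-score regression and add one prespecified adjusted model: the follow-up score on dose, with the baseline value of the same score, age, sex, symptom duration, baseline physical activity and reason for deselecting surgery as covariates. Report both dose slopes with 95% confidence intervals. State in advance that a dose association counts as supported only if the two models agree, for example when both intervals exclude zero on the same side, because neither is unbiased under every way that dose may depend on severity. Add that agreement does not rule out confounding by motivation or by symptoms that arise during treatment.

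Provider effects need no more than a sensitivity analysis, with a small-sample correction because there are only about ten clusters.

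The cost is a few degrees of freedom out of about 100 and one more model to report. No new data are needed. The Trial status section has data collection running to July 2026, so as of that section the wording could be fixed before the data are complete.

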### Implementation

We will conduct a multi-component examination of the implementation of the intervention, including process, fidelity, dose and reach [21]. We will examine the implementation process by describing the required structures and resources, and we will measure fidelity as the degree to which the intervention is delivered as intended. Dose will be measured as the number of completed supervised and home-based exercise sessions. High dose is defined as completing a minimum of 75% of scheduled training sessions, medium as completing 50–74% and low as completing less than 50% [21]. Additionally, we will measure the dose using the exercise adherence rating scale (EARS) [29, 30]. Reach will be examined by describing baseline participant characteristics in those receiving a high compared versus a low dose, and by comparing the age and sex of participants with those of non-participants. In an additional explorative analysis, we will examine if the dose is associated with changes in health outcomes.

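### The repeated-measures model for dose by reason for deselecting surgery does not match the single six-month EARS value that Table 1 assigns to the question, and no dose measure has a baseline value

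*Protocol article*

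**What the plan says.** All references are to the protocol article.

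- **Question.** Table 1, Acceptability (explorative), asks: "Does the reason for deselecting surgery moderate dose". The section Acceptability of the intervention also speaks of dose. Quantitative data analysis instead asks whether the reason "moderates dose changes as part of the examination of acceptability".
- **Data for the question.** Table 1 gives the dose entry as "Self-report: exercise dose Six months", and its footnote identifies the instrument as the "Exercise Adherence Rating Scale". The other dose rows of Table 1 show the same source and time point. The section Data sources refers the reader to Table 1 for timing and for the link between sources and questions.
- **Model.** "in a repeated measurement analysis using a mixed-effects model, an explorative analysis will be undertaken", with participants as random effects and "a fixed factor for group and time and the corresponding interaction (group × time), adjusted for baseline values".
- **Definition of dose.** The section Implementation says: "Dose will be measured as the number of completed supervised and home-based exercise sessions". It adds EARS as a further measure. Its categories ("High dose is defined as completing a minimum of 75% of scheduled training sessions", with medium and low below that) give one summary per participant. Participant training records says that completed sessions are entered in a weekly logbook.
- **Baseline data.** Online participant survey lists the baseline process variables. None of them is a dose.
- **Population.** Overarching research design says that process data come from the intervention group. Table 1 gives about 100 participants.

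**The concern.** The stated model needs repeated values of the outcome and some baseline value. The source assigned to the question supplies one value, taken at the end. Dose here means adherence to a programme that has not begun at baseline, so a pre-intervention dose does not exist.

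Three wording problems add to this. The outcome shifts from dose to change in dose. Group is not defined, although all process data come from one trial arm. A difference in dose between two reasons is called moderation, although moderation would mean that the reason alters the effect of one variable on another, and no such effect is specified.

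As the text stands, the outcome, the time axis and the baseline term would have to be chosen later, possibly with the data in view and with a significance threshold of 0.05 already declared. A result obtained that way could not be traced to a prespecified analysis, even an explorative one.

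**Working it through.** The article gives no figure for this analysis, so there is none to reproduce. The check is whether the stated terms can be estimated from each possible dose source.

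**Inputs.** Outcome y is dose. g is the reason (surgeon's or participant's decision). t is time. There are 100 intervention participants (Table 1). EARS is measured once, at six months (Table 1). Sessions are logged weekly (Participant training records). Six months is taken as 26 weeks, which is an assumption. Data were simulated only to test identifiability, and the simulated coefficients say nothing about the trial.

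**Model as stated.**

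y_it = b0 + b1·g_i + b2·t + b3·g_i·t + b4·y_i0 + u_i + e_it, with var(u) = τ² and var(e) = σ².

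**A. EARS at six months only.** Time takes a single value T, so the model without the baseline term becomes

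y_i = (b0 + b2·T) + (b1 + b3·T)·g_i + (u_i + e_i).

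- Fixed effects: only the two bracketed sums can be estimated. The design matrix with columns 1, g, t and g·t has rank 2 of 4. Time is aliased with the intercept, and group × time with group.
- Variances: the data carry only τ² + σ². With the total held fixed and the participant share set to 0, 25, 50, 75 and 99%, the log-likelihood was −288.14 each time. The random effect is not identifiable.
- Baseline dose: with the two estimable terms plus a pre-intervention dose equal to 0 for everyone, the rank is 2 of 3. The covariate adds nothing.
- Entering a structural zero for everyone as an extra baseline outcome row makes the fixed design formally full rank (4 of 4). The baseline difference between reasons is then 0 by construction, so the group × time coefficient is simply the six-month difference in dose, and the baseline rows carry no information.

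**B. Weekly logbook counts, 26 per participant.**

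- The design with columns 1, g, week and g·week has rank 4 of 4, and the random-intercept model converged. Reason × time and the participant effect can be estimated.
- Adding a baseline dose of 0 for everyone gives rank 4 of 5. That term still fails.

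**Side by side.**

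| Term in the stated model | EARS, six months (Table 1) | Weekly logbook (not assigned to this question) |
|---|---|---|
| Time | no | yes |
| Group × time | no | yes |
| Participant variance | no | yes |
| Baseline dose | no | no |

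**What a single-value comparison could detect.** The estimable model under A is intercept plus reason. Assuming a two-sided 5% level, 80% power and a normal approximation, the detectable standardised difference is (1.960 + 0.842) × √(1/n1 + 1/n2). The splits between reasons are assumptions.

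- 50 and 50: 2.802 × √(0.0200 + 0.0200) = 0.56
- 30 and 70: 2.802 × √(0.0333 + 0.0143) = 0.61
- 42 and 43 (the minimum of 85 in the arm): 2.802 × √(0.0238 + 0.0233) = 0.61
- 26 and 59: 2.802 × √(0.0385 + 0.0169) = 0.66

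Only differences of about 0.56 to 0.66 standard deviations would be detected reliably. That favours an estimate with its confidence interval over a significance test.

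**The case against.** The strongest reply is that dose is not measured only once. The section Implementation defines dose first as completed sessions and brings in EARS as an addition, and the sessions are logged weekly. The references to repeated measurement and to change in dose fit that record well. This stands: a reader might infer that the planned analysis cannot be run on any data in the trial, and the article does not support that. It does not remove the contradiction, because Table 1 assigns EARS at six months to this question, no passage names the logbook as this model's outcome, and time is left undefined.

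A second reply is that the phrase on baseline values need not mean baseline dose. It could mean covariates such as baseline physical activity, which is collected. That also stands as a possible reading, but no covariate is named. On the usual reading, adjustment for the baseline value of the outcome, the term has nothing to use.

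Third, the analysis is explorative, acceptability is examined mainly through interviews, and the separate trial protocol, which is not shown, may describe dose recording more fully. The first two parts limit the severity. The third does not help, because the problem is a conflict between two statements in this article rather than a missing detail.

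A reader might also suppose that the model was meant for a health outcome and would be run on HAGOS or iHOT-12 and reported as a finding about dose. Nothing in the article says so. The objection to the word moderation is one of terminology, and the comparison intended is still recognisable.

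**Conclusion.** The point holds as a mismatch between a stated model and its stated data source. With EARS at six months, time, group × time and the participant variance are not identifiable: 2 of 4 fixed effects can be estimated, and the likelihood is flat in the split of variance. A baseline-dose term fails for EARS and for session counts alike. With weekly counts the rest of the model can be fitted.

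The conclusion assumes that Table 1 governs which source answers which question, as the article says it does. The baseline part also assumes that baseline values means baseline dose. The rank results do not depend on the simulated values, and the logbook result needs only repeated weekly entries, not exactly 26.

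This is a should-fix. It concerns one explorative question in the process evaluation and leaves the main randomised comparison, its sample size and its analysis untouched.

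**What to change.** Choose one of two routes and make Table 1 and Quantitative data analysis agree.

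- **(a) One value per participant.** Use a linear regression of six-month EARS, of the percentage of scheduled sessions completed, or of each separately, on the reason for deselecting surgery. Report the mean difference with its 95% confidence interval. Drop time, group × time, the random effect and the baseline-dose term. If the percentage is used, add the logbook to this row of Table 1.
- **(b) Course of dose over time.** Name weekly logbook session counts as the outcome in both places, define time (for example, week since the start of the programme), and fit reason, time and reason × time with a participant random effect and no baseline-dose term.

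Under either route, state that group is the reason for deselecting surgery within the intervention arm, use either dose or change in dose consistently, and describe the result as an association with dose. Covariate adjustment is optional. If it is wanted, name the covariates.

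The cost is a few sentences and one table row. No new data are needed. The Trial status section reports 76 of 200 participants enrolled in January 2024, with data collection planned until July 2026, so on that timetable the change can be recorded before the data are complete.
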